## Abstract

**Background:**

Early conduct problems and school failure are prominent risk factors for several adverse outcomes in later life. With the potential of reaching many children at early stages of their life, school-based interventions constitute a valuable approach to universal prevention. Good behavior game (GBG) is a promising school-based behavior management program, having shown immediate reductions in conduct problems along with several long-term positive effects. Adapting interventions to new contexts may however affect their effectiveness. The current study aims to evaluate the effectiveness of a Swedish adaption of GBG under pragmatic conditions. The intervention is hypothesized to reduce conduct problems in the classroom (primary outcome). Secondary analyses will investigate changes in conduct problems in common school areas, classroom climate, teacher collective efficacy, on-task behavior, as well as investigating behavioral management practices, implementation, and barriers to implementation.

**Methods:**

This is a cluster-randomized trial with two parallel groups. Schools will be randomized (1,1, stratified by their areas sociodemographic index score) to be provided training in GBG or perform business-as-usual. The intervention and data collection lasts for a school year. Data will be collected at three time points: at baseline in the beginning of the school year (prior to training in GBG), after three months, and after nine months (at the end of the school year; primary endpoint). Data consists of teacher-rated measures of conduct problems, classroom climate, teacher collective efficacy, behavior management practices, and implementation factors, along with demographic factors. In addition, data will be collected by independent and blinded observers using corresponding measures in a subset of randomly chosen classrooms. Procedural fidelity will be rated and collected by GBG-trainers during nine observations throughout the school year. Statistical analysis will include frequentist intention-to-treat analysis, and comparisons of estimates with a corresponding Bayesian model using weakly informative priors. The study has currently completed data collection.

**Discussion:**

This study will provide knowledge in universal prevention and school-based interventions with high reach, as well as specific knowledge concerning the effectiveness of an adapted version of GBG under real-world conditions, along with factors affecting its implementation and effects.

**Clinical trial registration:**

ClinicalTrials.gov, identifier NCT05794893.

## Introduction

1.

Preventive interventions in schools have the potential to teach skills and create nurturing environments for many children over a long course of time. School-based interventions can yield positive effects on social and emotional skills, mental health, externalizing behavior, and academic skills (1). Due to their potentially high reach, these interventions can include many children in a cost-effective way (2). Furthermore, these interventions can be launched and delivered before the onset of students’ difficulties, e.g., conduct problems (3). One such established approach to school-based universal prevention is good behavior game (GBG) (4). GBG is a behavioral management program for younger school children that utilizes game-like features, such as teams, objectives, and a scoring system, in order to foster skills that are conducive to self-regulation and task-oriented classroom environments. The intervention is manualized and integrated by teachers in their regular teaching activities.

Previous studies have shown that GBG reduces children’s conduct problems in comparison to control interventions (5). Conduct problems as defined here are patterns of behaviors in which the basic rights of others or major age-appropriate societal norms or rules are violated, such as aggression (6). The prevalence of conduct problems varies considerably depending on study and sample, but even early-onset or life-course persistent conduct problems, the classifications associated with highest risk and severity, are reported to include 8%–25% of all children (7–10). Barring the most direct consequences for the individual and immediate environment, conduct problems increase the risk for symptoms related to anxiety and depression in childhood (11). These internalized symptoms, along with conduct problems, are linked to school failure (12, 13). Long-term, the presence of conduct problems in childhood increases the odds of mental health issues, aggression, criminality, higher consumption of alcohol and cannabis, poorer general health outcomes, as well as poorer educational and occupational outcomes in adulthood compared to individuals with low levels of conduct problems in childhood (14, 15). Following this logic, reducing conduct problems in childhood should reduce the risk of multiple adverse outcomes in a longitudinal perspective. Consequently, early prevention such as GBG has demonstrated positive effects all the way to young adulthood, including reductions in suicide ideation, substance use, and violent and criminal behavior, compared to control interventions (16–19). Taken together, research points to GBG as a promising preventive intervention across diverse student populations (20).

Despite earlier demonstrations of efficacy in one setting, positive effects are not guaranteed when transferring to new settings. For example, GBG was evaluated in a randomized controlled trial in England with no immediate main or subgroup effects (21). One explanation could be that a new setting needs a specific adaptation in order to retain efficacy (22). Likely attributable to multiple factors (23), it is not uncommon for interventions to lose efficacy when attempting replication outside the original site (24). Implementation is likely also a critical factor for success (25, 26), which may be influenced by contextual factors when implementing GBG and similar interventions (27). Implementation may be further compromised in a natural, or non-research, setting as adaptations are made reactively, e.g., due to lack of time and resources (28). Taken together, there is an apparent need to evaluate GBG under local and naturalistic circumstances. As such, the intention for this study is to conduct a pragmatic type of trial under local real-world conditions, rather than an explanatory study under ideal circumstances (29). In this case, the intention is to evaluate GBG when it has been entirely funded, chosen, translated, adapted, and implemented by a practically oriented organization and infrastructure, with the research group entering later in the process and attempting to minimize its influence. Consequently, this is the first randomized controlled trial of GBG with an explicit focus on being a pragmatic trial. See the PRECIS-2 table provided in Supplementary Table S1 for additional details regarding the trial’s pragmatic orientation.

The primary objective is to evaluate the effects of GBG-training on decreasing conduct problems in elementary school classrooms as compared to schools conducting business-as-usual (BAU). The secondary objectives are to evaluate the effects of GBG-training on conduct problems in common school areas, classroom climate, collective teacher efficacy, behavioral management practices and on-task behavior. With GBG compared to BAU, teacher-rated conduct problems in the classroom are expected to decrease at both 3- and 9-month follow-up. Conduct problems in common school areas are only expected to decrease at 9-months follow-up since relevant generalization components in GBG are implemented after the 3-month follow-up. It is also hypothesized that observer-rated measures will corroborate corresponding teacher-rated measures. The role of sociodemographic factors and implementation as moderators will be investigated. In addition, the role of contextual factors as possible barriers and facilitators for adoption and implementation will be investigated.

## Methods and analysis

2.

### Design

2.1.

The study is a parallel group, cluster-randomized controlled superiority trial. Schools will be chosen as the unit of randomization to minimize contamination effects and to follow the municipality’s chosen strategy for implementation. This chosen strategy implements GBG in all K–3 (typically corresponding to children aged 6–9) classrooms simultaneously in every included school, rather than allowing for implementation in single classrooms in different schools. The group ratio will be 1:1 and randomization will be stratified using an aggregated sociodemographic index score used by the municipality to allocate school funding.

As the study and intervention lasts for a Swedish school year (August to June the following year) randomization will be conducted in May, before the end of the preceding school year. This is to ensure that schools have a similar amount of time to prepare for GBG as corresponding to their usual practice, as well as allowing the research group time to prepare all schools for data collection procedures. Randomization will be conducted and implemented by the research team. After recruitment all schools will be stratified as higher or lower than the city average on the stratification variable, i.e., the municipality’s sociodemographic index score, which has a centered mean at 100. Following this procedure, schools will be assigned a computer-generated number between 0 and 1 using the statistical software SPSS (RRID:SCR_002865), where schools with the highest numbers in each stratum will be placed in the intervention group. The research group will then notify schools of their study allocation, which will either be the intervention group who will receive training in GBG, or the control group, who will be conducting BAU. Schools in the control arm will be offered GBG-training in the following school year as an incentive to participate. GBG will be conducted by teachers who receive training during the study from certified GBG-trainers provided by the municipality.

Measurements will primarily be concentrated along three timepoints, with each data collection period being limited to three weeks: Baseline (T1), 3-month follow-up (T2), and 9-month follow-up (T3 – primary endpoint). This corresponds to training in GBG which is spaced within the duration of a Swedish school year. Baseline measurements will be conducted post-allocation, just before start of training and intervention, to ensure the inclusion of all newly enrolled students. Data is primarily collected through teacher-rated, observer-rated, and trainer-rated measurements, though trainer-rated measures are collected continuously and not constricted to the 3-week measurement periods. A list of measures and their sequence are summarized in the SPIRIT-figure (Figure 1). All measures are collected on a classroom level. The study will be set at Sweden’s third largest municipality (Malmö), who is currently piloting the preventive framework Communities That Care (CTC) (30). See the trial registration on ClinicalTrials.gov (NCT05794893) for more details on study sites.

### Selection of subjects

2.2.

To follow usual practice for the intervention, eligible schools are those with students in grades K–3. Exclusion criteria consist of schools where classrooms are already implementing GBG or schools who primarily have special education classrooms. However, inclusive classrooms using the standard Swedish curriculum with a few students receiving special education may still be included.

Recruitment will also follow usual conditions for the municipality, which in this case means that recruitment will be headed by trainers and facilitators working with CTC. The intervention and consequent participation in the study will first be offered to eligible schools in pilot areas for CTC. Schools with matching risk and protective factors according to CTC will be prioritized. Due to GBG already being implemented in several pilot areas, only a few schools are expected to sign up at this phase. As such, recruitment will be broadened in a second stage where GBG and participation in the study is offered to all remaining eligible schools in the municipality. Interested schools will then be jointly assessed for eligibility by the municipality and the research group. In the case of unsuccessful recruitment, other geographically close municipalities could be included in the recruitment phase.

In order to maximize statistical power for this sample, the number of recruited schools need to remain at the municipality’s maximum capacity for simultaneously implementing GBG, which is roughly 3–5 new schools at the time of the study for the intervention group. This corresponds to approximately 450–750 students based on typical school and class sizes in the area. It is important to note that this sample size was judged as acceptable with an earlier design and power analysis for this study that included individual level variation. However, this power analysis has not been updated for the current design that measures primarily on a classroom level, which is likely to yield lower statistical power, even with the intervention group at full capacity.

### Interventional methods

2.3.

In 2015, the Swedish municipality of Malmö launched a process of exploring and adapting GBG to a Swedish context for use within a general preventive framework (CTC). While GBG is American in origin, several versions have been studied both domestically and internationally since its inception (31, 32). To ensure the closest fit, the municipality opted for a version adapted and studied in a Dutch-speaking context (33–35). There are some notable adaptations in the Dutch version of GBG compared to the contemporary American version (from American Institutes for Research) it was based on, such as students encouraging each other in behaving appropriately, and teachers not mentioning student’s rule violations (34). When developing the Swedish version, the intention was to keep adaptations on a surface level, rather than changing deep structure. As such, only a few adaptations were made in adapting the Dutch version to a Swedish context, besides translation. Most notably, rewards are less focused on tangibles and more on desired activities compared to the Dutch version. Some minor changes were also made to increase fit to the Swedish school year. The complete Swedish adaptation (named “Höjaspelet”) has been tested in a pilot study, but without a control group and with high attrition (36).

GBG (Höjaspelet) is a teacher-driven and manual-based behavioral management program for the classroom. It is played out like a game using interdependent groups. The game is integrated with regular classroom teaching. Based on teacher observation and assessments of student’s shyness and rule infracting behavior, students are divided into balanced teams. Each team customizes their name and poster to be used for the game. Each session the teams receive a set of cards representing points. The game starts with three rules, which are formulated as positively stated and observable behaviors (e.g., “Raise your hand to speak,” “Work independently” or “Share with your classmates”) and paired with visual aids. During the game, the teacher frequently delivers behavior-specific praise contingent on students or groups following the rules. Rule infractions prompt the teacher to remove a point card from the team discreetly, but otherwise ignoring the infraction rather than reprimanding. Teachers are encouraged to maintain at least a 4:1 praise-to-reprimand ratio. After the game, all teams that still have at least one card are included in a reward. Teachers are encouraged to ensure that all teams can and should win, e.g., by increasing the number of point cards available. Wins are tallied on each team’s poster.

The intervention is divided into an introductory phase, expansion phase, and generalization phase. The phases are ordered sequentially and last about 3 months each, with the introduction phase being somewhat longer and the generalization phase being somewhat shorter. The class is divided into new teams prior to each phase. The function of the different phases is to gradually generalize new behaviors outside the game context. This is generally done by increasing game time and fading out components of the game (e.g., fewer, and more delayed rewards). Game time is set to gradually increase during the introduction phase, from 10 min to about 45 min. With the help of transition supports and breaks, the game time may increase to as much as 3 h during the expansion phase.

Game time does not necessarily increase during the generalization phase, instead focus is placed on incorporating components of GBG outside the specified game time. For example, the generalization component of this phase may entail teachers still referring to three rules and delivering praise contingent on adhering to the rules, while maintaining a 4:1 praise-to-reprimand ratio. At the same time, the teacher should remove the usage of teams, their respective posters, and their point cards. At first, this method of generalization is only used for about 5 min immediately following a regular game session. As the phase progresses, it is conducted during longer periods of time, and not necessarily as a direct extension of a regular game session. Teachers are also prompted to have students discuss and share reflections regarding the game once in a while during this phase.

The number of game sessions is set to 3 times a week during all phases. This default format is designed to last for a school year with a class that is naïve to GBG, which is the focus of this study. Teachers may start the school year in a later phase when conducting GBG with students who already have experience with GBG.

Although this Swedish adaptation keeps GBG within the classroom environment, the municipality uses a school-wide implementation process, meaning all K–3 teachers within a school are required to receive training and implement the intervention simultaneously. Teachers receive about 3.5 h of group instruction prior to every phase. The trainers also observe the teachers approximately once per month (nine times in total during the school year), using a standardized form, and delivering feedback to the teacher after every observation.

All training in GBG is conducted by certified trainers in GBG employed by the municipality. The standard path to becoming certified as a GBG-trainer is by first becoming certified in conducting GBG in the classroom. After this, a person can be certified as an internal GBG-coach by observing and giving feedback on procedural fidelity at least twice in all three phases, accompanied by a certified trainer. The final step is to conduct training sessions together with certified trainers during a year of implementation before becoming a certified GBG-trainer, making the entire process approximately three years long.

The trainers in this trial will be a mix of trainers who have either been certified through the standard path by Swedish trainers or certified as the first generation by Dutch trainers which did not include the first certification, i.e., implementing GBG with fidelity in a classroom as a teacher. To become an independent site that could certify new teachers and trainers, the first generation of Swedish trainers were trained in the Dutch version of GBG by the CED Group Foundation (a non-profit organization).

As the study is designed to test the effectiveness of GBG under naturalistic conditions, BAU was chosen as a comparator as the objective is to compare GBG to existing behavioral management strategies that schools already have in place or will naturally implement.

Since the study follows naturalistic conditions, both in how the intervention is implemented, and how schools proceed without the intervention, the research group does not attempt to control teacher practice, e.g., implementing measures to increase fidelity or control concomitant care. No criteria are set for discontinuing or modifying any allocation from the research group. Teachers in the intervention group can modify or be noncompliant regarding the intervention, and teachers in the control group can attempt to use practices taught in GBG without training. For this reason, behavior management practices will be tracked in both arms. It will primarily be up to schools and training staff to ensure implementation in the experimental arm. The research group will not directly support implementation efforts in this study.

### Measures

2.4.

#### Teacher-rated measures

2.4.1.

One teacher from each included class will respond to a demographic questionnaire developed for the trial concerning the number of students in each class, number of boys (to assess gender distribution), number of students where Swedish is a secondary language, number of students (partially or wholly) excluded from ordinary classroom activities, additional staff in the classroom, and experience with the current class. Demographic items are assessed at T1 and T3. The intervention group receives two additional items at T3 regarding the number of GBG-sessions they had the previous week and if they expect that they will continue using GBG during the next school year.

##### Conduct problems

2.4.1.1.

The primary outcome for this study is conduct problems in the classroom. This will be measured using the scale “Problem Behavior in the Classroom Last Week,” listing 20 items concerning conduct problems commonly found in school classrooms, e.g., verbal assault directed towards other students, disturbing or distracting other students, and physically assaulting other students. A secondary outcome is conduct problems in school environments, which will be measured using the scale “Problem Behavior in the School Environment Last Week.” The scale remains similar to its classroom counterpart and consists of 15 items concerning conduct problems experienced in school common areas. For both scales, the teacher bases their ratings on the week prior to assessment and rates all items on a scale from 0 (no times last week) to 4 (several times a day). Both scales were translated from Norwegian to Swedish and have shown sound psychometric properties in previous Norwegian studies, with internal consistency at α = 0.88 and α = 0.84 for the respective classroom and school environment scales (37–39). Conduct problems will be assessed at all three time points.

##### Teacher collective efficacy

2.4.1.2.

Teachers will rate 12 items on a collective efficacy scale. The scale concerns the perceived efficacy of teachers in the school, as a collective, being able to teach all students attending the school or if they experience considerable barriers. It revolves around factors such as teachers not being able to motivate students, students’ sociodemographic factors being too difficult to overcome, or that teachers in the school do not possess the necessary skills to deal with problem behaviors. Items are rated on a 0–5 Likert scale and were translated to Swedish from a Norwegian version of the scale (38, 40). Internal consistency ranged from α = 0.82 to 0.85 in a Norwegian sample (41). The scale will be assessed at T1 and T3.

##### Classroom environment

2.4.1.3.

To assess classroom environment, teachers will rate 14 items on the Classroom Environment Scale. The scale concerns the learning climate in the classroom (e.g., cooperation between students, if students are task-oriented or if students are engaged). Items are rated on a 0–3 Likert scale. The scale has been translated from Norwegian to Swedish. Internal consistency ranged from α = 0.83 to 0.85 in the most recent Norwegian sample (39). The scale will be assessed at T1 and T3.

##### Behavior management practices

2.4.1.4.

Behavioral management practices will be assessed using 22 items that represent an assortment of behavioral management practices that may be used by teachers in the classroom (e.g., giving praise to students for desired behaviors, using harsh reprimands, and practicing social skills). The items are divided into the scales Positive Behavior Support and Behavioral Correction. Items are rated on a scale of 0–6, ranging from using a certain strategy 0 times to using it more than 20 times, all during the last 30 days. The items were developed in Norway and translated to Swedish. The Norwegian sample supported the use of the two factors Positive Behavior Support (α = 0.74 to 0.76 using nine items) and Behavioral Correction (α = 0.57 to 0.66 using eight items) (41). The instrument will be used at T1 and T3.

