The lack of restrictions in this pragmatic trial also increases the importance of tracking behavioral management practices in the control group. Usual care or practice has a history of only being vaguely defined and controlled for (52). The efficacious behavioral management practices found in GBG could potentially be more widely disseminated among teacher staff in this sample compared to previous studies, e.g., due to generally increased knowledge or teacher mobility within the municipality. To address this, behavioral management practices will be tracked in both groups by independent observers and teacher-rated measures.

The study design poses some methodological considerations, most notably the reduction in statistical power by the limited sample size and classroom-level variables. An earlier version of the study used individual-level variables (with a corresponding three-level power analysis) in conjunction with consent forms where parents could actively opt-out their children from the data collection, similar to the design used by the English GBG-trial (53). However, the Swedish Ethical Review Authority required active consent from all parents. This prompted a change in design to remove individual-level variables as there were major concerns with attrition using active consent forms, particularly in areas with lower socio-economic status. Further, any potential changes had to be made rapidly as preparations and implementation of GBG need to be timed accordingly to the school year, and the pool of local eligible schools is expected to reduce for each implementation cycle. This also precluded the inclusion of an updated power analysis corresponding to the new design and pre-registering the study before recruitment. This limitation should be considered in light of the difficulties in achieving suitable sample sizes in highly pragmatic conditions. A potential benefit is that the current design is relatively low-cost and lightweight, making it suitable for pragmatic aims. This may encourage more trials when organizations import or develop interventions before scaling up, which could be a significant investment considering each trainer require at least three years of development in this case. Newer interventions may however still need large trials under ideal conditions to first determine efficacy.

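### The 30-day recall window of the behavior-management items probably reaches into the summer break at T1 but not at T3, so within-arm T1–T3 change on these scales cannot be read as changed practice

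*Protocol article*

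**What the plan says.** Section 2.4.1.4 of the Protocol article describes 22 items on classroom behavior-management practices, scored 0–6 and grouped into a positive-support scale and a correction scale. The rating is a count over a fixed period: "ranging from using a certain strategy 0 times to using it more than 20 times, all during the last 30 days". On timing, "The instrument will be used at T1 and T3".

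The Abstract (Methods) places T1 "at baseline in the beginning of the school year (prior to training in GBG") and T3 "after nine months (at the end of the school year; primary endpoint"). Section 2.1 Design gives the school year as August to June and puts baseline "just before start of training and intervention, to ensure the inclusion of all newly enrolled students". It describes the measurements as timed "with each data collection period being limited to three weeks".

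Section 2.3 says practices are tracked in both arms because control teachers may try GBG practices without training. The Discussion says that the trial's lack of restrictions "increases the importance of tracking behavioral management practices in the control group". Section 2.5 models the primary outcome with a group-by-time interaction and sends the secondary outcomes to broadly similar linear models.

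**The concern.** A teacher can use classroom practices only on days when school is in session. A count over the last 30 calendar days therefore depends on how many of those days were teaching days. If T1 opens less than 30 days into term, early T1 respondents report on a window that is partly holiday. At the end of the school year the whole window lies in term. The same practice then earns a lower score at T1 than at T3, on both scales and in both arms.

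The control arm is where this matters most. A rise there on the positive-support scale could look like spread of GBG-type practice, and could be offered as an explanation for a null primary result. A rise on the correction scale could look like more reprimanding over the year. In the GBG arm the same artifact would add to apparent uptake.

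**Working it through.** The plan gives no figure to reproduce on this point, so the check has three parts: how much of the T1 window is in term, what that does to an unchanged score, and what it does to the between-arm contrast.

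**1. Share of the T1 window in term.** From the documents: a 30-day window, a three-week collection period, nine months between T1 and T3, T3 at the end of the school year, and a year from August to June. Assumed: T3 is the last 21 days of the year, and nine months is 274 days. For a school year of L days, T1 opens on day L − 21 − 274. A teacher answering on day d of term has min(d, 30)/30 of the window in term. Averaging over the 22 values of d from opening to opening + 21:

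| L (days) | T1 opens on day | Mean share in term |
|---|---|---|
| 295 | 0 | 35% |
| 300 | 5 | 52% |
| 305 | 10 | 68% |
| 310 | 15 | 82% |
| 320 | 25 | 98% |

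The first row is not realistic. The conduct-problem scales in the same T1 collection ask about the preceding week (2.4.1.1), which presupposes about a week already taught. Opening on day 7 gives a mean share of 58%.

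A second check used assumed calendar dates: term starting 1, 16 or 31 August, T3 closing 1, 15 or 30 June, and T1 273 days before T3. Eight of the nine combinations give some overlap with the break. Three of those eight would open T1 before term starts and should be set aside. Of the remaining six, five overlap, with a mean of 0.7 to 10 pre-term days per window. In the central case (16 August, 15 June) T1 opens 10 days into term, the mean overlap is 10 days (a share of about 67%), and about 95% of response days are affected. Overlap vanishes only if T1 opens 30 or more days into term.

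**2. Effect on an unchanged score.** The article gives only the end categories, so equal bins are assumed: 0; 1–4; 5–8; 9–12; 13–16; 17–20; more than 20. Uses are taken as Poisson with mean λ per 30 term days, and λ × share at T1. The spurious rise is the expected score at λ minus the expected score at λ × share:

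| λ | Share 50% | Share 70% | Share 90% |
|---|---|---|---|
| 10 | 1.25 | 0.75 | 0.25 |
| 15 | 1.86 | 1.11 | 0.37 |

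Away from the ends of the scale this is close to λ(1 − share)/4, because each bin spans four uses. For λ = 10 and a share of 58% it is 10 × 0.42/4 ≈ 1.05.

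The artifact depends on frequency. Comparing 10 with 21 teaching days in the window, under three assumed sets of cut-points, the rise is about 0.7–0.9 points at 0.25 uses per day, 1.4 at 0.5 per day, 1.7–2.5 at one per day and 0.6–0.8 at two per day. It is about 0 at three or more per day, where the top category is reached both times. A practice never used stays at 0.

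**3. Between-arm contrast.** With equal baselines and equal completion dates, the same rise occurs in both arms and cancels in the interaction. With arms at 10 and 15 uses and no change in either, it does not: 1.86 − 1.25 = 0.61 points at a 50% share, and 1.11 − 0.75 = 0.36 at 70%. If one arm answers a week later at T1, the share moves by 7/30, for example from 50% to 73%. At 10 uses this shifts the T1 score by about 0.58 points.

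**The case against.** The planned analysis is a between-arm comparison of change, and both arms share one municipality's school calendar and the same collection periods. The artifact therefore largely cancels, and nothing in the article suggests that completion dates differ by arm. This stands. What remains is conditional: a baseline difference is plausible with about 3–5 schools in the intervention arm (2.2), and a proportional shrinkage of T1 scores does not cancel when baselines differ.

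A reader might infer that the plan intends to interpret a control-arm T1–T3 rise as spread of GBG practices. The article does not say so. It says practices are tracked, and T3 levels alone could serve that purpose. The point is that the article leaves the faulty reading open while stressing the control arm.

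A reader might also infer that reprimands and praise cannot be judged any other way. In fact the blinded observers count general praise, behavior-specific praise and corrections over 20 minutes (2.4.2), at each of the three time points and with no 30-day window. That is a real check, but only in the observed classrooms and for those behaviors.

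The size is uncertain. No T1 date is given, the bins are assumed, and frequent practices such as praise may sit at the ceiling at both times. All of this stands, so the size is a range that depends on frequency, and not a shift of the whole scale.

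**Conclusion.** The mismatch follows from the article's own recall period and timing, and nothing shown rescales the window by teaching days or places T1 a month into term. Within-arm T1–T3 change on the two behavior-management scales is therefore not interpretable as it stands for practices of low to middle frequency. Under equal bins and 10 uses per 30 term days, the spurious rise is about 0.25–1.25 points for in-term shares of 90–50%. The top of that range needs T1 to open about five days into term. These figures rest on the assumed dates, cut-points and Poisson counts.

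The documents do not support a claim that the treatment effect on these scales is biased as such. The group-by-time contrast is largely protected and is exposed only to baseline or completion-date differences between arms. Nor is the primary outcome affected, since its recall period is one week. This is a worthwhile change to a secondary analysis, not a threat to the trial's main conclusion.

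**What to change.** For the two behavior-management scales, compare arms on the T3 score with the T1 score as covariate, keeping the stratum term and the allowance for clustering. This uses an estimated slope for T1 where a change analysis implicitly fixes it at 1, so a common shrinkage of T1 scores is largely absorbed. If completion dates were recorded, add the number of teaching days in each T1 window, taken from the school calendar, as a further covariate.

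Describe control-arm practice by T3 levels and by the blinded observers' praise and reprimand counts. State that within-arm T1–T3 change on these scales will not be read as change in practice or as spread of GBG practices.

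A count model with teaching days as an offset is not needed. It would require category cut-points that the article does not give, and is out of proportion for a secondary measure with so few schools.

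Data collection is complete (section 5), so the T1 window itself cannot be altered. The change is in analysis wording, with a calendar lookup if dates exist, and needs no new participant data. The cost is giving up a within-arm change reading on a secondary measure.
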